##### 2.6.2.11. Sleep quality

Pittsburgh Sleep Quality Index (PSQI, Spanish version) will be used to measure quality and patterns of sleep over the past month (89). It differentiates between “poor” and “good” sleep by measuring seven domains: subjective sleep quality, sleep latency, sleep duration, habitual sleep efficiency, sleep disturbances, use of sleep medication and daytime dysfunction. It consists of 19 self-applied questions and five questions that request the evaluation of the patient’s bedmate or roommate (these are not scored). The sleep quality levels include good sleep quality (0–5) and poor sleep quality (6–21). The validated Spanish version has a Cronbach’s alpha value (α) of 0.81 (90).

##### 2.6.2.12. Physical activity

International Physical Activity Questionnaire-Short Form (IPAQ-SF, Spanish version) will be used to measure levels of habitual physical activity over the last 7 days (91). It has seven items and records the activity of four intensity levels: vigorous-intensity activity, moderate-intensity activity, walking and sitting. A total physical activity result MET (minutes/week) can be calculated as the following: total physical activity is the sum of the total results (walking + moderate + vigorous) MET. The Physical Activity levels include low (0-600 MET), moderate (601-3000 MET), high (more than 3000 MET). The validated Spanish version has a kappa value (k) of 0.70 (92).

##### 2.6.2.13. Consumption of tobacco and narcotic substances

Examination of the frequency of consumption of substances such as tobacco and narcotics will be carried out through an *ad hoc* questionnaire prepared by the research team measured with the 4-question scale adapted from the WHO MONICA study (91, 92). It will assess the current consumption or time since the last consumption, starting age, type of substance consumed and the specific amount of each substance.

### 2.7. Data analysis

Baseline analysis of the results: Descriptive analysis of all variables (percentage and confidence interval for qualitative variables; means and standard deviation for parametric quantitative variables or median and interquartile range for non-parametric quantitative variables) and univariate analysis (we will use the T-Student for parametric quantitative variable, Mann-Whitney U for non-parametric quantitative variables, and the Chi-Square test for qualitative variables) to evaluate the differences between the patients who have some of the most prevalent affective-emotional problems in primary care (anxiety, depression) compared with those who do not. Statistical analyses will be chosen based on the size of the sample (parametric or non-parametric tests). To compare the two groups, missing data will be assessed and the need to use an intention-to-treat (ITT) analysis and a multiple imputation (MI) technique to handle missing data will be assessed.

To answer the main objective, we will use a multiple linear regression model. To do this, each main variable, the PHQ-9 score, BDI-II, GAD-7, PGBQ, AUDIT, and MULTICAGE-ICT, will be used as a continuous variable. Multiple linear regression will be performed using a stepwise method to obtain a better fit result to the statistical analysis. This stepwise regression simply will repeat the multiple regression, each time removing the least correlated variable. Only the significant variables obtained in the bivariate analysis will be entered into the regression model.

Finally, mediation/moderation analyses will be carried out to analyze whether psychological constructs participate as a mediator or as a moderator in the association of lifestyles (exposure) and anxiety, depression and/or addictions (outcome). The PROCESS analytical tool developed by Hayes will be used to assess mediation/moderation. These analyses were based on multiple linear regression path analysis (93). Bootstrap resampling (10.000 samples) will be used to estimate 95% confidence intervals. Given that heteroscedasticity is common in cross-sectional data, all analyses will include a correction for heteroscedasticity (HC0) (94). The Johnson-Neyman technique will be used to compute the range of significance and simple slopes for the interaction analyses (93). We will report unstandardized regression coefficients; all analyses will be two-tailed and used conventional significance thresholds (α = 0.05). Data collection and statistical analysis will be performed using Excel software, SPSS software (version 25.0) (95) and the statistical software environment R (version 3.6.2) (96).

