Our main objective in this study is to analyze the relationship between psychological constructs (self-efficacy, activation, health literacy, resilience, personality traits, sense of coherence, self-esteem), affective-emotional problems (anxiety, depression) and addiction in primary health care. Therefore, our main hypothesis is that subjects with lower levels of the psychological constructs (self-efficacy, activation, health literacy, resilience, sense of coherence, self-esteem) will have more severe depressive, anxious, and addictive behavior symptoms than those with higher values of the psychological constructs.

One of the secondary objectives of this study is to analyze whether these psychological constructs act as mediating or moderating factors in the relationship between the diagnosis of comorbidities or healthy lifestyles and depression, anxiety, and addictive disorders. Therefore, our secondary hypothesis is that the relationship between the diagnosis of comorbidities or healthy lifestyles and depression, anxiety, or addictive disorders will change according to the value of the different moderators, such as self-efficacy, activation, health literacy, resilience, personality traits, sense of coherence, and self-esteem.

Moreover, a final secondary objective is to create a cohort for an analysis of the relationship between these psychological constructs and lifestyles and the incidence rate of diagnoses of depression and/or anxiety to be revisited after 5–10 years. Consequently, our last secondary hypothesis is that people with lower levels of the psychological constructs and less healthy lifestyle habits will be more likely to experience increased incidence of diagnoses of depression and anxiety or worsening symptoms in the following 5 to 10 years than will those with higher values of the psychological constructs of healthy lifestyles.

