##### 2.6.2.9. Health-related quality of life

The European Quality of Life-5 Dimensions Questionnaire (EQ-5D, Spanish version) will be used to measure health-related quality of life. It will be used to calculate the quality-adjusted life year (QALY) during the monitoring period by adjusting the length of time affected by the health result in relation to the utility value (85). It contains five health dimensions (mobility, self-care, usual activities, pain/discomfort and anxiety/depression), and each of these has three levels (no problems, slight or moderate problems, and severe problems). Moreover, this questionnaire incorporates a Visual Analog Scale (VAS) which can be used as a quantitative measure of health outcome reflecting the patient’s own judgment. Patients mark the point on the vertical line that best reflects their assessment of their current global health status. In its Spanish version, the Cronbach’s alpha coefficient is 0.78 (86).

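### The main-objective regression makes correlated constructs compete, protects none of them and does not exclude other measures of the outcome, so a construct that satisfies the hypothesis may be dropped or strongly attenuated

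*Protocol article*

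**What the plan says.** The main hypothesis (Protocol article, 1. Introduction) concerns six constructs: self-esteem, resilience, health literacy, sense of coherence, self-efficacy and activation. It predicts that people who score lower on them "will have more severe depressive, anxious, and addictive behavior symptoms than those with higher values of the psychological constructs". It does not claim that each construct contributes independently of the others.

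Section 2.7 assigns this question to one analysis: "To answer the main objective, we will use a multiple linear regression model". For it, "each main variable, the PHQ-9 score, BDI-II, GAD-7, PGBQ, AUDIT, and MULTICAGE-ICT, will be used as a continuous variable".

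Predictors are chosen in two steps. Entry: "Only the significant variables obtained in the bivariate analysis will be entered into the regression model". Removal: "This stepwise regression simply will repeat the multiple regression, each time removing the least correlated variable". The only bivariate step described is a set of univariate tests "to evaluate the differences between the patients who have some of the most prevalent affective-emotional problems in primary care (anxiety, depression") from those who do not. It comes directly after a "Descriptive analysis of all variables".

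The section gives no list of candidate predictors for this model, forces in no construct or confounder, and excludes nothing. Section 2.6.2.9 says of EQ-5D: "It contains five health dimensions (mobility, self-care, usual activities, pain/discomfort and anxiety/depression"). Section 2.6.1.1 measures depression with both PHQ-9 and BDI-II.

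**The concern.** The hypothesis and the model ask different questions. The hypothesis asks whether symptom severity differs between people low and high on a construct. The coefficient in the final model asks whether that construct adds anything once every other surviving variable is held fixed. The constructs are related psychosocial traits. If they are positively correlated, each can satisfy the hypothesis while few survive the pruning, and which ones survive depends partly on chance.

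A second exposure comes from what the rule leaves open. The variables most likely to differ between people with and without anxiety or depression are measures of anxiety and depression. Read literally, the rule would admit EQ-5D, and BDI-II and GAD-7 in a PHQ-9 model. Holding a second measure of the outcome fixed removes much of the relation under study.

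At stake is the study's main result: true relations may be missing from the reported model, and the coefficients that remain do not estimate the hypothesised lower-versus-higher difference.

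**Working it through.** **Inputs from the article.** Six hypothesised constructs; two-sided alpha 0.05; a required sample of 290 with 30% withdrawal allowed for, which leaves 290 × 0.70 = 203. Table 2 totals 395. The article gives no figure for the performance of this model, so there is none to reproduce. The derivation of 290 is a separate matter; it is used here only as a sample size.

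**Assumptions.** The article gives no correlations. Take a construct-outcome correlation r of 0.2 to 0.3 in absolute value and equal correlations ρ among the six constructs of 0.3 or 0.5, with multivariate normal data. The removal threshold is not stated; p>0.05 is assumed. The screen is simplified to a test of each construct against the continuous outcome.

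**Step 1: size of the coefficient.** With six equally correlated constructs, the standardised joint-model coefficient is r/(1+5ρ). For r=0.30:
- ρ=0.3: 0.30/2.5 = 0.12
- ρ=0.5: 0.30/3.5 = 0.086

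Each construct's relation with the outcome is still 0.30; only the conditioning has changed.

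**Step 2: retention under the planned sequence.** Simulation of the screen at p<0.05 followed by backward removal, as the percentage of runs in which a truly related construct is kept. The low end of each range is r=0.2, the high end r=0.3.

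| N | ρ | Kept by screen plus removal | Significant in full joint model, no removal |
|---|---|---|---|
| 290 | 0.5 | 26–41% | 12–23% |
| 290 | 0.3 | 40–63% | 24–53% |
| 203 | 0.5 | 22–34% | 10–17% |
| 203 | 0.3 | 33–54% | 17–39% |

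Tested singly at N=290, each construct is detected in 91–100% of runs. On average the procedure keeps between 6 × 0.26 = 1.6 and 6 × 0.63 = 3.8 of six constructs that all satisfy the hypothesis. The last column shows that simply omitting the stepwise removal does not cure the problem. What matters is which variables are held fixed.

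**Step 3: sensitivity to the assumptions.** With stronger relations (r 0.3 to 0.4, ρ 0.3 to 0.6), retention with constructs only is 33–87% at N=290, and 28–95% across N=203 to 395. Single tests detect 99–100%.

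**Step 4: if an outcome-like measure also entered.** This is conditional, since the article does not say it will happen. For a covariate correlated c with the outcome and r with the construct, the construct's coefficient is (r − r·c)/(1 − r²). With r=0.3:
- c=0.5: (0.30 − 0.15)/0.91 = 0.165
- c=0.75: (0.30 − 0.225)/0.91 = 0.082

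Under the Step 3 assumptions at N=290, adding an EQ-5D-like variable (correlation 0.6 with the outcome) lowers retention to 19–64%. Adding two rival symptom scales as well (0.70 to 0.75) lowers it to 8–14%.

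**The case against.** A reader might infer that the plan conditions on EQ-5D and rival symptom scales, and that related constructs will be declared unrelated. The article supports neither. The six symptom scales appear in section 2.7 only as dependent variables, the stated use of EQ-5D is health-related quality of life and QALYs, and the phrase about all variables belongs to the descriptive analysis. A condensed article may also leave the candidate list to a fuller plan. No rule says that removal from the model means no relationship, and at N=290 at least one construct was kept in essentially every run.

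The planned univariate comparison would also show unadjusted associations with anxiety or depression status. That is real evidence on part of the hypothesis, but it does not use continuous severity, does not cover the addiction scales, and is not the analysis assigned to the main objective.

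Finally, mutual adjustment of related psychosocial predictors is a recognised exploratory approach, and the objective speaks only of a relationship. That justifies keeping a joint model. It does not make a pruned joint model a test of the lower-versus-higher contrast. The entry and removal rules are stated in the article, so this is more than omitted detail.

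**Conclusion.** The point holds in a limited form. The stated rules protect no construct, force correlated constructs to compete, and do not exclude alternative measures of the outcome. A construct that meets the main hypothesis may therefore be dropped or have its coefficient strongly attenuated. Under the assumptions of Step 2 at N=290, the chance that a related construct is kept is about 26–63%, against 91–100% when tested singly. The size depends on correlations the article does not give and on an assumed removal threshold; with stronger relations and larger samples retention can reach 95%. The further loss from an outcome-like predictor is a risk that the wording leaves open, not a stated plan. This should be changed, because it affects the main objective and costs little.

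**What to change.** In section 2.7:

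1. For each outcome, make the main-objective analysis one model per construct with a fixed confounder set, such as age, sex, rural or urban area, and education, chosen without bivariate screening or stepwise removal.
2. State that EQ-5D and the other depression and anxiety scales are not predictors in the PHQ-9, BDI-II and GAD-7 models, and that the other addiction scales are not predictors in the addiction models.
3. Keep a joint model with all constructs as a secondary analysis of unique contribution.

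This needs only analysis wording and more regressions on data already to be collected; no participants or visits are added. There are two costs. Single-construct coefficients overlap and must not be read as independent effects. The number of tests rises to at least 6 constructs × 6 scales = 36, and more if personality traits or the five MULTICAGE-ICT scales are analysed separately. Results should therefore be reported as estimates with confidence intervals, under a stated approach to multiplicity.

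### The main-objective regression lets p-values choose among constructs that were named in advance, so retained coefficients tend to be exaggerated

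*Protocol article*

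**What the plan says.** The Introduction's main objective is to study how three sets of variables are linked: "psychological constructs (self-efficacy, activation, health literacy, resilience, personality traits, sense of coherence, self-esteem), affective-emotional problems (anxiety, depression) and addiction in primary health care". The main hypothesis is directional: "subjects with lower levels of the psychological constructs (self-efficacy, activation, health literacy, resilience, sense of coherence, self-esteem) will have more severe depressive, anxious"; the sentence goes on to cover addiction. The exposures are thus fixed before any data are seen.

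Section 2.7 then says how the objective will be answered. Six scores are the dependent variables: "each main variable, the PHQ-9 score, BDI-II, GAD-7, PGBQ, AUDIT, and MULTICAGE-ICT, will be used as a continuous variable". The model is built by selection: "Multiple linear regression will be performed using a stepwise method to obtain a better fit result to the statistical analysis". Deletion works as follows: "This stepwise regression simply will repeat the multiple regression, each time removing the least correlated variable". Entry is restricted: "Only the significant variables obtained in the bivariate analysis will be entered into the regression model".

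The only group comparison described, in the preceding paragraph of Section 2.7, is between "the patients who have some of the most prevalent affective-emotional problems in primary care (anxiety, depression) compared with those who do not". The article labels it univariate and does not define bivariate analysis. It states no rule that keeps a construct or a confounder in the model, and no threshold at which deletion stops.

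**The concern.** Selection by significance may suit a search for predictors, but here the exposures are known and the task is to estimate and test them. Two mechanisms then bias what is reported.

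- A construct is reported only if its estimate in this sample is large enough to be significant, so reported estimates lean high.
- When a correlated construct is dropped, part of its effect shifts onto those that remain. Self-efficacy, resilience, sense of coherence and self-esteem can be expected to correlate.

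The usual confidence interval accounts for neither. The same rule can remove age, sex or urban/rural residence, the variables on which Section 2.4 stratifies the sample.

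The undefined screen adds a second risk. If the anxiety/depression comparison is the screen for all six models, a construct related to alcohol, gambling or ICT use but not to affective disorder could be shut out of the models meant to test it.

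**Working it through.** **Inputs from the article.** The six outcomes and the selection rules are in Section 2.7. There are seven constructs, which make 6 + 5 = 11 scores if the five BFI-10 factors are counted separately (Introduction, Table 3). The significance level is 0.05, two-sided (Section 2.7). Section 2.4 gives n = 290 and planning prevalences of 3.1% and 4.8%. The article gives no figure for the performance of the selection procedure, so there is none to reproduce.

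**Assumptions, not in the article.** Constructs are standardised and equally correlated, four of them have equal true effects, 14 other candidates are unrelated to the outcome, and the deletion threshold is p < 0.05. Each candidate is screened against the outcome score itself, which is the reading more favourable to the plan.

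**Check 1: size of effect (n = 290, correlation 0.4–0.5).** Screen at p < 0.05, then backward deletion.

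| True effect | Inflation of retained estimate | Implied mean retained estimate | 95% CI coverage |
|---|---|---|---|
| 0.12 | 56–70% | 0.12 × 1.56 to 1.70 = 0.19–0.20 | 81–89% |
| 0.15 | 29–37% | 0.15 × 1.29 to 1.37 = 0.19–0.21 | 88–92% |
| 0.20 | 5–7% | 0.20 × 1.05 to 1.07 = 0.21 | about 95% |

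The third column shows the practical problem: the procedure reports about 0.2 whether the truth is 0.12 or 0.20. At least one irrelevant variable was kept in about 34–61% of runs.

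**Check 2: correlation and sample size.** Here there are 11 scores only, three with a true effect of 0.15, and the same selection.

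| n | Correlation | Mean retained estimate | Inflation | Coverage |
|---|---|---|---|---|
| 203 | 0 / 0.3 / 0.5 | 0.205 / 0.222 / 0.249 | 37% / 48% / 66% | 94.5% / 89.9% / 81.9% |
| 290 | 0 / 0.3 / 0.5 | 0.180 / 0.194 / 0.219 | 20% / 29% / 46% | 96.5% / 93.2% / 86.8% |
| 395 | 0 / 0.3 / 0.5 | 0.166 / 0.176 / 0.197 | 11% / 17% / 32% | 96.6% / 94.8% / 90.3% |

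Inflation is the mean retained estimate divided by 0.15, minus 1. The model with all 11 scores kept covered 94.9–95.1% in every row. The sizes 203 and 395 are 290 × 0.70 (the 30% withdrawal in Section 2.4) and the total in Table 2.

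**Check 3: if the screen is the anxiety/depression comparison.** The assumptions are two constructs related only to addiction (effect 0.3), two others related only to caseness (0.5), caseness of 5–20%, and n = 203 or 290. The addiction constructs entered the addiction model in about 5% of runs at correlation 0 and in 36–81% at correlation 0.3. The full model detected them in 95–99.9%.

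**Check 4: sensitivity of that screen.** Cases are 290 × 0.031 ≈ 9 and 290 × 0.048 ≈ 14, about 23 in all if the diagnoses do not overlap. The difference detectable with 80% power is 2.80 × √(1/23 + 1/267) ≈ 0.61 SD. With the 395 people of Table 2 and about 31 cases, it is 2.80 × √(1/31 + 1/364) ≈ 0.52 SD.

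**The case against.** **Stepwise selection is conventional, and the harm depends on the effect size.** This stands in part. At effects of 0.20, inflation is small and coverage nominal, and with uncorrelated constructs coverage is also near nominal. A reader might infer that the coefficients and intervals will be wrong. The article gives no effect sizes or correlations that would support so firm a statement. The direction of the bias is secure; its size is not.

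**Selection does not lose more true constructs than the full model.** This stands when each outcome is screened on its own score. At 0.12 and correlation 0.4, selection retained each true construct in 54% of runs, while the full model found it significant in 39.5%. Low retention at that effect size mainly reflects weak power, so it is no argument for the change.

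**The anxiety/depression gate on the addiction outcomes is an inference.** This stands. Section 2.7 calls the comparison univariate and places it in the descriptive paragraph. Screening each variable against its own outcome score is at least as natural a reading. What remains is an ambiguity, and it matters under one of the two readings.

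**Overlapping scales.** A reader might infer that BDI-II, GAD-7 and EQ-5D will be predictors in the PHQ-9 model. No section says so. Section 2.7 lists BDI-II and GAD-7 only as dependent variables there, so no loss from this source can be charged to the plan.

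**Case numbers.** It is tempting to quote detectable differences of 0.95 SD for depression (9 cases) and 0.77 SD for anxiety (14 cases). Those figures split what Section 2.7 describes as one comparison of two groups. Section 2.3 also cites higher primary-care prevalences, up to 12.2% and 11.3% in women, so cases may be more numerous than planned.

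**A confounder list may sit in the full protocol.** Agreed, and its absence from the article is not the point. The point is the stated rule, which allows any variable to be removed.

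**Conclusion.** The point holds. Section 2.7 fixes a significance gate and stepwise deletion for the analysis that carries the main hypothesis, although the exposures are named beforehand. Retained coefficients will tend to be exaggerated: slightly if standardised effects are near 0.20, and by about half or more if they are near 0.12. Interval coverage falls below nominal when effects are weak and constructs correlated. These magnitudes rest on assumed effects, correlations and a 0.05 deletion threshold, none of which the article gives. Inflation appeared in every setting of the first two checks and does not depend on whether 290 or 395 people are recruited.

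The gate on the alcohol, gambling and ICT models is conditional. It could exclude constructs related only to addiction if the anxiety/depression comparison is the screen meant, and the article does not settle this.

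**What to change.** Delete the bivariate gate and the stepwise step from Section 2.7. For each outcome, state one pre-specified linear model containing all named construct scores and a fixed confounder set from data already collected: at least age, sex and urban/rural residence, with education, socioeconomic status and comorbidity. Keep every term whatever its p-value, and report every construct coefficient with its interval. State that the other outcome scales are not used as covariates. Keep the comparison of people with and without anxiety or depression as descriptive, and label any stepwise model exploratory.

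The change rewrites a few sentences and needs no new data. About 20 parameters on about 290 people is feasible. The cost is somewhat wider intervals. It does not promise more power for weak effects: at a true effect of 0.12 and correlations of 0.4–0.5, the full model finds each true construct significant in only 34–40% of runs.

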### 2.4. Sample size and sampling

The sample size was computed using the formula for caclulating the population estimates of the most prevalent affective disorders in primary care (anxiety and depression) (69). To calculate the sample size, we will use the data obtained in the study by Santomauro et al. (57). We used the prevalence of the most frequent affective disorders and addictions in primary care (anxiety, depression) as the main variable: 3.1% for major depression and 4.8% for anxiety disorders. Accepting an alpha value of 0.05 and a margin of error of 3% of units, the total sample size required was 290 with the expectation of a possible 30% withdrawal rate.

n=Zα2⁢p⁢(1-p)e2

For selecting potential participants, stratified selection will be made by age, sex and population distribution in urban and rural areas with respect to the National Institute of Statistics data from the census of Aragon 2021 (Figure 1 and Table 1). This stratification will be carried out with the intention of establishing the greatest variability within the sample and reaching a maximum level of representativeness for the population (Table 2). To achieve this, different primary care health centers in the autonomous community, 1–2 rural centers and 1–2 urban centers, will be selected. The rural centers sampled will be in towns with a population of under 2,000 inhabitants.

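### HC0 in the mediation/moderation analyses makes interaction tests mildly to moderately liberal; HC3 is closer to the planned 5%, and the role of the bootstrap should be stated

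*Protocol article*

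**What the plan says.** The point lies in the second part of Section 2.7 (Data analysis), which covers the PROCESS mediation and moderation models for lifestyle exposures, psychological constructs and the outcomes. It fixes four things:

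- Variance estimator: "all analyses will include a correction for heteroscedasticity (HC0"), justified there by heteroscedasticity being common in cross-sectional data.
- Test level: "all analyses will be two-tailed and used conventional significance thresholds (α = 0.05").
- Interaction follow-up: "The Johnson-Neyman technique will be used to compute the range of significance and simple slopes for the interaction analyses".
- Intervals: "Bootstrap resampling (10.000 samples) will be used to estimate 95% confidence intervals". The text does not say which effects are judged by these and which by HC0 standard errors.

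The first part of Section 2.7, on the stepwise regressions for the main objective, names no variance estimator.

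One lifestyle exposure is IPAQ-SF activity, for which "total physical activity is the sum of the total results (walking + moderate + vigorous) MET" (Section 2.6.2.12). Its low band starts at 0 and its top band has no upper limit. No expected distribution is given for this or any other exposure.

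**The concern.** HC0 inserts raw squared residuals into the sandwich variance. A high-leverage observation pulls the fit towards itself, its residual shrinks, and the standard error becomes too small. Products of two scores create such observations, the more so if one score has a long tail.

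The secondary moderation hypothesis is tested on these product terms. Simple slopes and Johnson–Neyman regions come from the same coefficient covariance matrix. Where inference uses that matrix, moderators will be declared somewhat more often than the planned 5% when none exist, and regions of significance will be somewhat too wide.

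**Working it through.** **1. Sample size to use.** The article gives no error rate or power for the moderation tests, so the only figure to reproduce is N. Section 2.4 uses n = z²p(1−p)/e², with prevalences "3.1% for major depression and 4.8% for anxiety disorders" and "Accepting an alpha value of 0.05 and a margin of error of 3% of units". It concludes that "the total sample size required was 290 with the expectation of a possible 30% withdrawal rate".

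- p = 0.048: 1.96² × 0.048 × 0.952 / 0.03² = 195.05, so 196; 196/0.7 = 280.
- p = 0.031: 128.2, so 129; 129/0.7 = 184.3, so 185.
- p = 0.05: 202.8, so 203; 203/0.7 = 290.

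The stated 290 is matched only if 4.8% is rounded to 5%. Table 2 totals 395. The check therefore uses both 290 and 395.

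**2. Mechanism.** With constant variance σ², a residual with leverage h has variance σ²(1−h). HC0 uses e²; HC3 uses e²/(1−h)². For an illustrative h = 0.30, the HC0 contribution averages 0.70σ² and the HC3 contribution 0.70/0.49 = 1.43σ². HC0 is biased down, and HC3 can overcorrect. Average leverage is (number of parameters)/N, here 7/290 = 2.4% or 7/395 = 1.8%, so the bias comes from a few extreme points.

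The conditional effect at moderator value w is b₁ + b₃w, with variance V₁₁ + 2wV₁₃ + w²V₃₃. Johnson–Neyman limits therefore inherit any bias in V.

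**3. Type I error by simulation.** The model has an exposure, a moderator, their product and three covariates. The true interaction is 0, the reference is t, the test is two-sided at 5%, and there are 4,000 replicates per setting (Monte Carlo standard error √(0.05×0.95/4000) = 0.35 points). The exposure is normal, exponential or lognormal, the moderator normal or skewed, and the errors normal or skewed. The variance is constant or depends on exposure and moderator. All these distributions are assumptions. Selected settings, rejection in %:

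| N | Exposure / moderator / error / variance | Model-based | HC0 | HC3 |
|---|---|---|---|---|
| 395 | normal / normal / normal / constant | 4.9 | 6.0 | 5.0 |
| 290 | lognormal / normal / normal / constant | 5.2 | 9.1 | 5.2 |
| 290 | lognormal / skewed / normal / constant | 5.2 | 9.7 | 5.7 |
| 395 | lognormal / skewed / normal / constant | 5.4 | 9.2 | 5.5 |
| 395 | normal / normal / skewed / varying | 13.8 | 7.4 | 6.2 |
| 290 | lognormal / skewed / skewed / varying | 37.0 | 16.2 | 8.6 |
| 395 | lognormal / skewed / skewed / varying | 40.0 | 16.4 | 9.4 |

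Ranges over all settings:

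- HC0, constant variance, normal exposure: 5.5–6.7% (N=290), 5.5–6.6% (N=395).
- HC0, constant variance, skewed exposure: 6.1–9.7% (N=290), 5.7–9.2% (N=395).
- HC0, varying variance with skewed errors: 8.0–16.2% (N=290), 7.4–16.4% (N=395).
- HC3, constant variance: 3.6–5.7% (N=290), 4.2–5.7% (N=395).
- HC3, varying variance: 6.3–9.4% (N=290), 6.2–9.4% (N=395).

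**4. Consistency check.** The mean HC0 standard error divided by the true standard deviation was 0.73–0.96 at N=290 and 0.75–0.98 at N=395. A ratio of 0.884 (second row) moves the effective critical value to 1.96 × 0.884 = 1.733, a two-sided size of about 8.3% against 9.1% simulated. A ratio of 0.73 (sixth row) gives 1.431, about 15.2% against 16.2%. Bias in the standard error explains most of the excess. A separate simulation with 12 parameters at N=290 gave HC0 6.5–6.6% (normal exposure) and 7.7–9.4% (lognormal), against HC3 4.7–5.1% and 4.5–5.5%.

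**5. Power cost.** For an assumed interaction of 0.15 SD with constant-variance normal errors:

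| N | Exposure | HC0 | HC3 | Model-based |
|---|---|---|---|---|
| 290 | normal | 71% | 67% | 69% |
| 290 | lognormal | 66% | 55% | 61% |
| 395 | normal | 84% | 81% | 82% |
| 395 | lognormal | 79% | 71% | 76% |

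Against the model-based test, which holds its size here, HC3 loses about 1–6 points. Part of HC0's apparent advantage is its inflated size.

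**The case against.** The strongest defence is that HC0 is a recognised, consistent estimator and that the authors foresaw heteroscedasticity. This stands: in the heteroscedastic settings at N=290 uncorrected least squares rejected 13–37%, against 8–16% for HC0. The plan's choice is far better than no correction.

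The bootstrap may carry the inference. In simulation the percentile bootstrap for the interaction rejected 4.0–6.3% at N=290. If it decided every moderation effect, little of the concern would remain. The article does not say so, and Johnson–Neyman regions as ordinarily computed use the covariance matrix.

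The larger figures depend on assumed distributions. This also stands. An open-ended top MET band does not establish a strongly skewed exposure, and the diet and sleep scores are bounded (MEDAS 0–14 and 0–17, PSQI 0–21). For these the normal-exposure rows are the closer guide, and with constant variance the excess is only about 0.5–2 points.

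A reader might take the word all to extend HC0 to the main-objective regressions. The sentence stands in the mediation/moderation paragraph, and the stepwise paragraph names no estimator, so the article does not support that extension. A reader might also use 203 participants (290 less 30%) and find larger errors. Withdrawal over 5–10 years does not reduce a baseline analysis, and the article justifies HC0 by cross-sectional data.

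**Conclusion.** The point holds as a modest improvement to a secondary analysis. HC0 was liberal for the interaction in every simulated setting. With constant variance the test rejects about 5.5–7% with a normal or mildly skewed exposure and about 6–10% with a strongly skewed one. Only strong skew together with marked heteroscedasticity brings it to about 16%. These figures rest on assumed distributions and on N between 290 and 395. They apply where inference uses HC0 standard errors rather than bootstrap intervals.

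Three stronger conclusions might be inferred and are not supported. First, 16% is not the expected error rate; it is the upper end of the assumed settings. Second, HC3 does not fully restore 5%: it still rejected 6–9% under heteroscedasticity. It was closer to 5% in nearly all settings, not all; at N=395 with a normal exposure, skewed moderator, skewed errors and constant variance, HC0 gave 5.5% and HC3 4.2%. Third, HC3 is not free, because it costs some power and can be conservative (3.6% in one setting at N=290).

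**What to change.** In the mediation/moderation part of Section 2.7:

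1. Replace HC0 by HC3 for interaction tests, simple slopes and Johnson–Neyman regions, and for the regression-based tests of the mediation paths.
2. State which effects are judged by the 10,000-sample bootstrap intervals and which by HC3 standard errors, so that one method decides each effect.

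This needs one or two sentences and a software option, settled before analysis. The cost is slightly wider intervals and the few points of power shown above. No transformation or categorisation of MET-minutes is proposed: the scale includes 0, where a plain logarithm is undefined, and no benefit from either step has been shown.
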